## 3 INTRODUCTION

---

### 3.1 BACKGROUND INFORMATION

The novel coronavirus SARS-CoV-2, first reported in late 2019, is currently the cause of a global pandemic of the coronavirus disease 2019 (COVID-19). In Africa, COVID-19 has the potential to cripple the continent's fragile healthcare systems and be devastating economically. As of writing, there is no proven effective chemoprophylaxis, no proven anti-viral treatment, and no vaccine to mitigate or prevent infection with SARS-CoV-2. While the risk groups for severe COVID-19 identified in resource-rich countries are male, older adults, obesity, diabetes, hypertension, and people of any age with serious underlying medical conditions, little is known about risk factors in malaria-endemic countries. Africa has a relatively young population, but a high prevalence of people living with compromised immune systems, such as those with poorly controlled HIV infection, tuberculosis, or acute and chronic malnutrition. African populations are also more frequently exposed to infectious diseases, such as malaria, that may exacerbate or dampen the inflammatory responses associated with COVID-19.

Malaria is endemic in most of sub-Saharan Africa. In sub-Saharan Africa, young children often have acute (symptomatic) malaria when infected with *P. falciparum* parasites. Older children and adults living in areas of moderate to high malaria transmission often have asymptomatic circulating blood-stage *P. falciparum* parasites. It is unknown whether immune-modulation associated with symptomatic or chronic malaria infections are risk factors for the severity of COVID-19, or high viral load and longer duration of virus shedding, both potential contributors of onwards spread of SARS-CoV-2. Malaria is also one of the main causes of moderate and severe anaemia affecting the body's oxygen-carrying capacity and placing young children at risk of tissue hypoxia and severe COVID-19, and a contributor to malnutrition, potentially further compromising a child's ability to mount an efficient immune response to SARS-CoV-2.

Chronic malaria could also be potentially protective against severe COVID-19. Although asymptomatic infections have been recognised to induce a level of immunologic hypo-responsiveness that may impede the development of protective immune responses to other infections, including to SARS-CoV-2, a hypo-responsive immune system may also provide partial protection from severe COVID-19 if it reduces the risk cytokine storm syndrome resulting from hyper-inflammation. This has been observed with other respiratory virus infection. For example, malaria-induced immunomodulation has been shown to be protective against respiratory distress associated with influenza, in hospitalized children in Kenya. There is also some suggestion from murine models that malaria infection can lead to reduced clinical symptoms by reducing the recruitment of cellular inflammatory components to the lungs of mice infected with pneumovirus (to model infections with the human respiratory syncytial virus (hRSV)). However, viral control was also impaired, leading to increased viral dissemination.

Malaria could also potentially enhance the coagulopathy seen with SARS-CoV-2 infection, which can manifest as venous thromboembolism and arterial thrombotic complications (including pulmonary embolism and stroke), disseminated intravascular coagulation (DIC) with pulmonary haemorrhage and thrombosis. Thrombocytopenia is another potential feature of COVID-19 and is associated with worse outcomes. Malaria is also associated with a pro-coagulant state, with activation of the coagulation cascade, mediated by TNF-alpha and IL-6, proportional to disease severity. Thrombocytopenia develops in 60–80% of malaria cases, and lysis of activated platelets, along with

tissue factor released from damaged vascular endothelial cells, promotes the pro-coagulant state, similar to the proposed mechanism in COVID-19.

Some of the existing antimalarial drugs, including the 4-aminoquinoline antimalarials chloroquine, hydroxychloroquine, amodiaquine (AQ), its main metabolite desethylamodiaquine, and pyronaridine, another quinoline-related compound structurally related to chloroquine, exhibit significant antiviral activity against SARS-CoV-2 in some cell lines in-vitro ([name], Medicines for Malaria Venture (MMV), personal communications). This has generated a widespread interest that they may provide clinical benefits in COVID-19 patients. However, the evidence base is growing rapidly, and the small number of trials that have evaluated chloroquine or hydroxychloroquine in confirmed COVID-19 patients have yielded mixed results. Recent unpublished data from Epithelix using primary nasal epithelial cell lines also suggests that the anti-viral effects on SARS-CoV-2 of these quinoline antimalarials, unlike Remdesivir, may depend on the cell lines tested in-vitro ([name], personal communication at the WHO-Workstream 1 meeting (May 19, 2020). More cell culture data are expected to become available in the coming months.

## 3.2 PROBLEM STATEMENT AND JUSTIFICATION FOR THE STUDY

### 3.2.1 Is malaria a risk factor for COVID-19 disease severity?

The rationale for this study is three-fold. First, it is critical to determine whether malaria infection is found to be a positive or negative risk factor for severe COVID-19 or its transmission. Even small changes in the risk of severe outcomes due to coinfections could result in substantial changes in the impact and epidemiology of COVID-19 in LMICs. The resulting morbidity and mortality from the pandemic may expand beyond predominantly older adults and those with underlying risk factors (heart and lung disease, diabetes, obesity, immuno-compromised) to a broader age range that includes infants, children, and younger adults. Furthermore, it would suggest that successfully controlling malaria would be needed to control the COVID-19 epidemic as it may have a positive, mitigating effect on COVID-19 severity and transmission. It would reinforce the importance, and potential expansion of malaria control programs to avoid similar scenarios as during the Ebola outbreak and diversion of resources and antimalarials for COVID-19 treatment. By contrast, if partial immunosuppression from chronic malaria is found to be protective against severe COVID-19 resulting from hyper-inflammation, then aggressive malaria control such as mass drug administration may paradoxically increase severe COVID-19 in a subgroup of cases. We will, therefore, follow a cohort of COVID-19 patients with and without malaria with a primary objective, to understand better how co-infection of SARS-CoV-2 and *Plasmodium falciparum* impacts disease progression compared to COVID-19 patients without malaria.

### 3.2.2 Does co-infection with malaria affect the rate of seroconversion and/or seroreversion to SARS-CoV-2 infection?

Second, it is also unknown if malaria affects the type (IgG, IgA, IgM) or avidity of antibody response to SARS-CoV-2 infection and time to seroconversion and rate of loss of antibodies or seroreversion and quality (avidity) of antibody responses. Similar considerations will apply to immune responses to future COVID-19 vaccines and whether vaccine efficacy will differ in the presence of malaria parasitaemia and the subsequent clearance of these malaria infections by appropriate antimalarial treatment.

### 3.2.3 Does the choice of antimalarial treatment affect disease progression or the rate of seroconversion to SARS-CoV-2 infection?

Third, it is also important to know if the choice of antimalarial to treat malaria in co-infected patients affects the rate of seroconversion or disease progression. Most countries in sub-Saharan Africa, including Kenya and Burkina Faso, use artemether-lumefantrine as the first-line antimalarial for the case-management of uncomplicated malaria. Lumefantrine belongs to the group of aryl-amino alcohols like quinine, mefloquine, and halofantrine and does not have any anti-viral properties in-vitro ([name], MMV personal communication). Pyronaridine, as the artemisinin-based combination therapy (ACT) pyronaridine-artesunate (PA), is increasingly being rolled-out in sub-Saharan Africa as second-line treatment, or as an alternative to artemether-lumefantrine as part of a rotational or mosaic first-line treatment strategy to delay the onset of the development of drug resistance. It remains to be determined if antimalarial treatment with pyronaridine-artesunate provides any additional clinical benefit compared to treatment with artemether-lumefantrine in COVID-19 patients who are co-infected with malaria and require antimalarial treatment.

In humans, pyronaridine is slowly eliminated and has extensive tissue binding, including in the lung. PK/PD modelling suggests that pyronaridine when provided as a standard 3-day treatment course of pyronaridine-artesunate, could potentially provide 28 days of anti-viral cover based on their predicted pulmonary exposure ([name] and [name], personal communications, LSTM).

Assumptions of the study include that the in vitro effects of pyronaridine against SARS-CoV-2 will translate to an in vivo effect and a benefit in human

participants and that pyronaridine reaches concentrations in human tissues, including the lungs, that have a viral suppressive effect. However, the exact distribution of pyronaridine within the respiratory tract, and whether these in vitro findings will translate into clinical benefit, is unknown.

Quinoline antimalarials may also have unintended consequences in reducing the seroconversion rate to the SARS-CoV-2 virus. Importantly, chloroquine has been shown to markedly decrease the seroconversion rate in persons immunised with the rabies vaccine resulting in 70% lower antibody titres through its potent anti-inflammatory effects by downregulating the cell-mediated immune response through its interaction with Toll-like receptors and affecting lysosomal degradation.

This raises a question whether similar effects could occur with other quinoline antimalarials like pyronaridine when used for the treatment of malaria of COVID-19 patients. We aim, therefore, to determine if malaria is a direct or indirect risk factor for mounting an appropriate immune response to SARS-CoV-2 and whether this is affected by the choice of treatment.

*Figure 1 Predicted Pyronaridine exposure in plasma (red line) and lung (blue line). Plasma exposure based on reported pk parameters in the literature and lung exposure predicted as a ratio to plasma exposure based on PBPK modelling.*

[figure not shown]

### 3.2.4 Rationale for pyronaridine-artesunate

Pyronaridine has some similarity in structure to chloroquine, and similar antiviral activity in-vitro against SARS-CoV-2 compared to chloroquine and hydroxychloroquine. Pyronaridine is active against SARS-CoV-2 in Vero76 cell assays in vitro with plasma/blood EC50 0.7  $\mu$  ([name], MMV personal communication). Moreover, Physiologically Based Pharmacokinetic (PBPK) modelling suggests that pyronaridine has excellent lung penetration, with a Cmax lung/blood ratio of 44, supporting the exploration of pyronaridine as a potential antiviral drug for COVID-19. There is very little information about the antiviral activity against SARS-CoV-2 of artesunate, but because the artemisinin derivatives are eliminated from the body within hours, artesunate is unlikely to have a clinically relevant impact on viral replication. The inclusion of artesunate is driven by the availability of the approved fixed-dose combinations of pyronaridine-artesunate with established safety, tolerability and efficacy in malaria. Pyronaridine has also shown promise in protecting mice from Ebola virus infection and has potent immunomodulatory properties in-vivo in mice.

Shin Poong Pharm. Co., Ltd, the manufacturer of pyronaridine-artesunate (Pyramax®), will evaluate pyronaridine-artesunate for the treatment of SARS-CoV-2 infection in symptomatic outpatients with mild disease in South Africa (<http://www.koreabiomed.com/news/articleView.html?idxno=8200>). This is an exploratory, randomized, single-centre, open-label study of four different experimental treatment arms versus standard of care and scheduled to start later in 2020. Artesunate-amodiaquine (AS-AQ) is an alternative candidate, but discussions with the respective MoH's in Kenya and Burkina suggest a preference for pyronaridine-artesunate because of tolerance, availability in each country and intended roll-out as first or second-line treatment in parts of the country in 2020-2021. Furthermore, in Burkina Faso, the use of amodiaquine is restricted to Seasonal Malaria Chemoprevention (SMC) (in combination with SP). Lastly, pyronaridine is the only quinoline antimalarial that is not associated with QT prolongation, which is a potential advantage over chloroquine and amodiaquine, particularly when used for the treatment of COVID-19 in combination with other QT-prolonging drugs like azithromycin.

### 3.3 NULL HYPOTHESES

Our null hypotheses are:

1. Malaria is not a direct or indirect risk factor affecting COVID-19 severity, duration of disease, and viral shedding
2. Malaria is not a direct or indirect risk factor for mounting an appropriate immune response to SARS-CoV-2
3. Pyronaridine-artesunate does not affect the seroconversion rate to SARS-COV-2 or ameliorate disease severity and accelerate recovery from COVID-19 in malaria co-infected individuals, relative to the standard first-line therapy of malaria with artemether-lumefantrine.

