| 
 
To determine if malaria infection affects COVID-19 disease presentation and duration
 
                                                  | 
 
Symptoms and duration of COVID-19 by day-28 in cases with and without malaria
 
                                                                                                                                                                                                                                                                                           |
| 
 
To determine if malaria infection in COVID-19 patients alters the antibody response to SARS-CoV-2 infection
 
                           | 
 
Cumulative seroconversion rates* (total antibody, IgG, IgM, IgA) by days 7, 14, 21, 28, and total antibody, IgG, IgM, IgA antibody titres against SARS-CoV-2 by day-28 expressed as the geometric mean, maximum, and change from baseline
 
Seroreversion rates for IgG, IgM, IgA and geometric mean antibody titres against SARS-CoV-2 by month 3, 6 and 12
 
     |
| 
 
To determine if malaria infection in COVID-19 alters the inflammatory, genomic, and cellular immune responses to SARS-CoV-2 infection
 
 | 
 
Multiplex serum cytokine markers; Transcriptional profiling (gene expression) of whole blood; Fixed whole blood for T and B cell markers by day-28
 
                                                                                                                                                                                                                      |
| 
 
To determine if malaria infection in COVID-19 alters the viral load or duration of SARS-CoV-2 infection
 
                               | 
 
Median viral load of SARS-CoV-2 detected from mid-nasal swabs by PCR
 
Cumulative incidence of SARS-CoV-2 clearance (defined as the proportion of participants with negative nasal swabs) by days 7, 14, 21 and 28
 
Time to clearance of nasal SARS-CoV-2, defined as negative SARS-CoV-2 RNA PCR tests (swabs collected on days 1, 3, 7, 14, 21 and 28)
 
 |

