### 7.3 METHOD OF TREATMENT ASSIGNMENT

Balanced randomisation will be used using permuted block randomisation methods stratified by site (i.e. hospital or clinic) and by the presence of symptoms at enrolment consistent with COVID-19 (asymptomatic vs symptomatic). A statistician in the UK will generate the randomisation lists with the allocation sequence, which will be forwarded to the trial pharmacists based in Kenya and Burkina Faso who will then prepare sequentially numbered, sealed, opaque boxes or envelopes for each participant with the randomisation assignments. Contained within each of these envelopes or boxes will be the pre-packed investigational product. The opaque boxes/envelopes will be opened sequentially upon enrolment of a study participant in each site. Stratification by the presence of symptoms at enrolment is needed to ensure balanced distribution among the two study arms as the presence of symptoms is likely to be an important (known) predictor of the COVID-19 disease progression (the primary endpoint). Currently at least half of the COVID-19 cases identified in Kenya are asymptomatic, reflecting targeted screening of contacts and high-risk populations. Minimisation or distance randomisation using central randomisation services by internet is not feasible because of the unreliable internet connections and telephone services in some of the proposed sites.

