## 11.2.4 Analytical methods by type of endpoint measure

### 11.2.4.1 Binary endpoints

For single measurements of binary endpoints, including for the binary primary endpoints of the screening study (cross-sectional survey, source population), COVID-19 cohort study and the nested malaria treatment trial, a generalised linear model (GLM) with the log-link function and binomial distribution (log-binomial regression) will be used to compare endpoints between exposure groups (e.g. by malaria status at enrolment). Crude GLM models will have the predictor of interest (e.g. malaria status at enrolment) as the only predictor and 'study site' as covariates. Results will be expressed as the risk ratio (RR) with associated 95% CI. If the log-binomial regression models do not converge, the 'binreg' or 'difficult' options (in that order) will be specified in Stata. If all models fail to converge, log-Poisson regression with a sandwich variance estimator will be used. Because the effect of malaria on COVID-19 may be biased by predictors that are not equally distributed by other predictors of COVID-19 severity, such as age, we will also conduct adjusted analyses to determine whether the effect of malaria on COVID-19 is affected with the inclusion of additional covariables. For repeated measurements of binary endpoints, a generalised linear mixed model (GLMMIX) with the log-link function and binomial distribution (log-binomial regression) will be used.

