### 11.2.4.2 Continuous endpoints

Continuous endpoints will be summarised using the number of subjects (n), mean, standard deviation (SD), geometric mean (95% CI), minimum, median (50th percentile), 25th and 75th percentiles and maximum by treatment group. For continuous endpoints with single measurements, a GLM model with a normal distribution and identity link function will be used, with the stratification factors 'site' and 'presence of symptoms' as covariates in the crude models and with additional co-

variates in adjusted models. Results will be expressed as the mean differences with their two-sided 95% CIs will be derived from the GLM model. For continuous endpoints with repeated measurements, a GLMMIX with the identity function and normal distribution will be used.

Non-normally distributed data will be transformed to obtain an approximately normal distribution. For example, antibody titres to COVID-19 will be summarised by geometric mean (the Geometric Mean Titre or GMT) (95% CI) by group, and groups compared using the Geometric Mean (Titre) Ratio (GMTR, or GMR) and associated 95% CIs (see also 11.2.4.4, Immunological responses, below).

If variables do not attain a normal distribution after transformation, results will be expressed and the median and 25% and 75% percentile by group and compared using the Wilcoxon rank-sum test.

For the analysis of the disease progression and clinical scales including the WHO clinical progression scale and the FLU-PRO scales, we will use change scores (95% CI) defined as the mean difference between the score at enrolment and the score by defined timepoints, or the maximum score achieved.

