#### **11.2.5.2 Assessment of efficacy**

Similar approaches as for the COVID-19 cohort study will be used to assess treatment efficacy for binary, count and continuous data, using treatment arm as the main exposure variable of interest, and the stratification factors study site and presence of symptoms as co-variates in the crude analysis. Secondary analyses include covariate-adjusted analysis to determine whether the estimate of treatment-effect is affected with the inclusion of additional covariables, and per-protocol analysis, and sub-group analysis. Imputation for baseline missing covariates will be carried out before categorising. Assessment of the homogeneity of treatment effect by a subgroup variable will be conducted by a GLM with the treatment, subgroup variable, and their interaction term as predictors, and the P-value presented for the interaction term.

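### Section 11.2.4.2 as written adjusts single-measurement continuous endpoints for symptoms even in comparisons by malaria status, although malaria can itself cause symptoms

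*Protocol*

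**What the plan says.** Section 3.3 frames the first cohort null hypothesis as "Malaria is not a direct or indirect risk factor affecting COVID-19 severity, duration of disease, and viral shedding". The second hypothesis, on the immune response, is also worded for direct or indirect effects. Section 4.2 turns these into cohort objectives, among them "To determine if malaria infection in COVID-19 alters the viral load or duration of SARS-CoV-2 infection", and lists antibody titres by day 28 as geometric mean, maximum and change from baseline.

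Section 11.2.4 sets out methods by endpoint type:

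- **Binary (11.2.4.1):** "Crude GLM models will have the predictor of interest (e.g. malaria status at enrolment) as the only predictor and 'study site' as covariates".
- **Count (11.2.4.3):** study site is the only covariate named.
- **Continuous, single measurement (11.2.4.2):** a normal model "with the stratification factors 'site' and 'presence of symptoms' as covariates in the crude models".
- **Continuous, repeated (11.2.4.2):** "For continuous endpoints with repeated measurements, a GLMMIX with the identity function and normal distribution will be used", with no covariates named.
- **Continuous, still non-normal after transformation (11.2.4.2):** medians "compared using the Wilcoxon rank-sum test".

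Section 11.2.5.2 says of the nested trial: "Similar approaches as for the COVID-19 cohort study will be used to assess treatment efficacy for binary, count and continuous data". It then names site and presence of symptoms as covariates for the treatment comparison. Section 7.3 defines presence of symptoms as a stratum of the trial's randomisation.

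**The concern.** In the nested trial, symptoms at enrolment precede randomisation and define a stratum, so adjusting for them is correct. In the cohort the exposure is malaria, and symptoms at enrolment may already be its result. Section 3.1 says young children with parasites often have symptomatic malaria. Section 7.2.1.1 describes nausea, dizziness and headache as hard to tell from acute malaria, and all three are items of the Flu-PRO scale in section 16.5.

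Two problems follow. First, a model that holds symptoms fixed does not estimate the direct-or-indirect effect that section 3.3 asks about. Second, if symptoms also reflect the SARS-CoV-2 infection, the symptomatic stratum compares unlike people. Malaria-negative members are symptomatic from COVID-19, while some malaria-positive members are symptomatic from malaria with a silent SARS-CoV-2 infection. A difference can then appear without any malaria effect.

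The adjustment would also differ by endpoint type for the same exposure: a day-28 titre would be symptom-adjusted in its crude model, and seroconversion from the same assay would not. At stake are single-measure titre summaries (day 28, maximum, change from baseline) and change scores on the clinical scales, when compared by malaria status.

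**Working it through.** **1. The plan's own figures.** No sample size is given for a continuous endpoint; section 11.1.1 supplies the group sizes. For 45% against 30%, ratio 1:4 and two-sided 5%, the pooled proportion is (0.45 + 4 × 0.30)/5 = 0.33.

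n(malaria+) = [1.960 × √(1.25 × 0.33 × 0.67) + 1.282 × √(0.45 × 0.55 + 0.30 × 0.70/4)]² / 0.15² = (1.030 + 0.702)²/0.0225 = 133.4, so 134.

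That gives 670 completers, and 670/0.95 = 706 enrolled (stated: 673 and 708). At 80% power it gives 99 × 5 = 495 completers and 522 enrolled (stated: 522). The plan's figures are reproduced within rounding, so 135 and 538 completers are used below.

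**2. Inputs for the check.** From the protocol: 135 malaria-positive and 538 malaria-negative completers. Assumed: 50% are symptomatic from COVID-19, set from "Currently at least half of the COVID-19 cases identified in Kenya are asymptomatic"; malaria alone makes a share q of carriers symptomatic; the outcome (SD 1) differs by d between people with and without COVID-19 symptoms; malaria has no effect on the outcome. The protocol gives neither q nor d.

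**3. Expected malaria coefficient with symptoms in the model.** Among people without symptoms the groups are alike. Among symptomatic people, all malaria-negatives have COVID-19 symptoms, but only 0.5/(0.5 + 0.5q) = 1/(1 + q) of malaria-positives do. The within-stratum gap is therefore −d·q/(1 + q). Least squares weights each stratum by (n₁ × n₀)/(n₁ + n₀).

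Example, q = 0.5 and d = 0.75:
- Symptomatic: n₁ = 135 × 0.75 = 101.25, n₀ = 269, weight 73.6.
- Asymptomatic: n₁ = 33.75, n₀ = 269, weight 30.0.
- Coefficient = −0.75 × (0.5/1.5) × 73.6/103.6 = −0.18 SD.

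**4. Type I error.** Approximate SE = √(residual variance / sum of weights). In the example the residual variance is 1 − 0.75²/4 = 0.859, plus about 0.019 because symptomatic malaria-positives are a mixture (0.75² × 0.5/1.5² × 101.25/673). So SE = √(0.878/103.6) = 0.092 and z = 0.178/0.092 = 1.93. The rejection rate is close to Φ(1.93 − 1.96), about 49%; simulation with 2,000 cohorts gives 47%.

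| q | d (SD) | coefficient (SD) | type I error |
|---|---|---|---|
| 10% | 0.25 | −0.01 | 5–6% |
| 20% | 0.5 | −0.05 | 7–8% |
| 30% | 0.5 | −0.07 | about 13% |
| 50% | 0.75 | −0.18 | about 47% |
| 70% | 1.0 | −0.33 | about 95% |

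Without the symptom term the simulated error is 4% to 6%. For scale, 135 against 538 gives 80% power for (1.960 + 0.842) × √(1/135 + 1/538) = 0.27 SD.

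**5. A different mechanism.** Let symptoms follow a logistic model with one odds ratio for malaria and one per SD of the outcome. Under no malaria effect the error is 6.6% (1.5 and 1.5), 17% (2 and 2), 44% (4 and 2) and 92% (9 and 3). If either odds ratio is 1, the error stays at 4.6% to 5.8%. If the outcome correlates only 0.5 with the cause of symptoms, the last three figures fall to 8.7%, 16% and 38%.

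**The case against.** The strongest reply is that the sentence is trial text. Section 11.2.4.2 summarises continuous endpoints by treatment group and speaks of stratification factors, which only the trial has. Section 11.2.5.2 names symptoms separately for the trial, which suggests they were not meant for every cohort model. That is a fair reading of intent. But the sentence sits in the shared section and carries no restriction. Because 11.2.5.2 already covers the trial, the only added effect of the words in 11.2.4.2 is on the malaria comparison. The ambiguity is a reason to correct the text.

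A reader might go further and infer three things that the documents do not support:

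- **That every continuous endpoint is affected, viral load included.** The covariate is named only for single measurements. Serial viral load falls under the mixed model, where none is named, or under the Wilcoxon test.
- **That a false malaria effect will appear.** It needs symptoms to depend both on malaria and on the titre or score. Section 7.3 calls symptoms a predictor of disease progression, not of viral load or titre, and section 3.1 says older carriers are often asymptomatic. With weak links the error is near nominal.
- **That the cohort's main result is compromised.** The progression endpoint used for the sample size is binary, and its crude model carries site only.

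It is also true that dropping symptoms does not guarantee an unbiased estimate. If asymptomatic cases were one third as likely to be enrolled (an assumption), the logistic settings 2/2, 4/2 and 9/3 give errors of 6.7%, 13.5% and 35% without the symptom term, against 18%, 53% and 96% with it.

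**Conclusion.** The point holds in limited form. Followed literally, section 11.2.4.2 conditions comparisons by malaria status on a variable that malaria can cause. This applies to single-measurement continuous endpoints and contradicts both the total-effect hypotheses of section 3.3 and the site-only crude models of 11.2.4.1 and 11.2.4.3. The mismatch with section 3.3 needs no assumption beyond malaria causing some symptoms. The false-positive risk does: it runs from about nominal to about 95% over the assumed links, and the protocol offers no figure to choose among them. The distortion can also run the other way, by hiding a real indirect effect. The consequence is confined to secondary titre summaries and clinical-scale change scores. It is worth correcting before analysis, but it does not threaten the study.

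**What to change.** In section 11.2.4.2, state that presence of symptoms is a covariate only in comparisons by randomised treatment, as section 11.2.5.2 already provides. For comparisons by malaria status, use site in the crude model, and add age and other factors not caused by malaria in the adjusted model. If a symptom-adjusted or symptom-stratified result is wanted, report it as a labelled sensitivity analysis. Carry the same wording into the SAP.

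The cost is one sentence and slightly more residual variance in the cohort models. Any bias from symptom-dependent testing or enrolment remains and should be acknowledged when the results are interpreted.
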